#### Outcome measures

For disability, we will use the I-RODS and the INCAT-DS. The I-RODS is a patient self-report linearly weighted scale that measures activity and social participation limitations [12, 15]. The I-RODS consists of 24 questions and allows for three response options: (0) impossible to perform, (1) performed with difficulty and (2) easily performed. Scores range from ‘0’ (all activities impossible to perform) to ‘48’ (all activities easily performed). These scores are transformed and expressed in log-odds (logits), ranging from − 6.95 to 8.11. The I-RODS has been developed specifically for inflammatory neuropathies including CIDP and has been validated in a large group of patients [16]. In addition, disability will be measured using the adjusted INCAT-DS, which has been used in numerous CIDP trials [5, 13, 17]. The adjusted INCAT-DS is a 10-point ordinal scale measuring limb disability, ranging from ‘0’ (no arm or leg disability) to ‘10’ (no arm movement possible, wheelchair bound). The reason to choose both disability scales to assess improvement and remission is outlined in the discussion. We will use a handheld Vigorimeter to measure grip strength in kPa, the Medical Research Council (MRC) sum score of 12 predefined muscle groups (including shoulder abduction, elbow flexion, wrist extension, hip flexion, knee extension and foot dorsiflexion) to measure muscle strength, the INCAT- sensory sum score (INCAT-SS) to assess sensory impairment, the Rasch-built Fatigue Severity Scale (R-FSS), the Pain intensity numeric rating scale (PI-NRS) and the EuroQol (EQ-5D-5L) to measure HRQL [18–24]. Health care resources will be measured using working documents and the iMTA Medical Consumption Questionnaire (*i*MCQ) and the Productivity Cost Questionnaire (*i*PCQ), both adapted to the study population [25, 26]. Working documents keep track of IVIg use, outpatient hospital consultations, hospitalizations, and major diagnostic examinations and therapeutic interventions. Tailored *i*MCQ will be used to measure volume of out-of-hospital consultations (general physician, physical therapist, psychologist, etc.), other institutionalizations (temporary rehabilitation, nursing home), day-care treatment, emergency admissions and out-of-pocket expenses by patients. The impact of CIDP on the ability of a person to perform work, production loss following absence from work or personal inefficiencies will be measured with the *i*PCQ. AEs reported spontaneously at visits or otherwise reported by patient or observed by physician, during the first 24 weeks of the study, or in the case of an early endpoint during treatment protocol within 6 weeks of last treatment course, are recorded using an AE template provided by the Amsterdam UMC, Clinical Research Unit (CRU). The AE template consist of a description, severity score (mild, moderate, severe), potential relation to IMP (unlikely, unlikely, possible, probable, definite, not possible to assess), consequences for IMP administration (options including temporary or permanent stops, dose changes), any other actions taken (i.e. start of co-medication, a referral) and the outcome (i.e. resolved). Severity scores will be defined as followed: mild (i.e. an AE that is transient and may require only minimal treatment or therapeutic intervention; the event does not generally interfere with usual activities of daily living), moderate (i.e. alleviated with specific therapeutic intervention; the event interferes with usual activities of daily living, causing discomfort but poses no significant or permanent risk of harm to the research patient) or severe (i.e. an AE that interrupts usual activities of daily living, or significantly affects clinical status, or may require intensive therapeutic intervention). Patients will complete a structured questionnaire with most frequent corticosteroid and IVIg-related AEs at the 18-week visit. These AEs are subsequently scored by the investigator using the previously described severity score. (S)AEs are further described under the ‘Adverse event reporting and harms {22}’ section. Long-term corticosteroid related AEs are also assessed by the investigator at weeks 52 and 104. AE questionnaires are completed after all other outcome assessments have been performed. Patients are asked to indicate which treatment they think they have received, at the end of the study. Outcome measures and assessment visits are listed under the ‘Plans for assessment and collection of outcomes {18a}’ section and shown in Table 1.

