### Sample size {14}

There are no robust figures on the long-term remission rates in patients treated with IVIg only. In a previous trial, remission during a 6-month period was seen in about half of IVIg responders, compared to 100% in IVMP responders [9]. However, a significant proportion of patients were not treatment naïve but known responders to IVIg. Furthermore, follow-up was shorter than the follow-up period in this study. We assume that the remission rate after IVIg is approximately 35% during an 8-month follow-up period. Treatment-naïve CIDP patients treated with dexamethasone had a long-term remission rate of 56% using a more stringent definition of improvement compared to this study [5, 8]. Our limited prospective pilot data of the OPTIC protocol suggest similar remission rates (59%) [10]. We assume remission rates of 35% in the IVIg/placebo group, and 65% in the IVIg/IVMP. A 30% difference in remission rate is large but warranted as IVMP may lead to various AEs in patients and because there is the alternative of continuing maintenance IVIg treatment. A two-group chi-square test with a 0.05 two-sided significance level will have 80% power to detect the difference between a control group proportion (IVIg/placebo) of 0.35 and a treatment group proportion (IVIg/IVMP) of 0.65 (odds ratio of 3.45) when the sample size in each group is 43 (86 patients in total). Anticipating on a 10% attrition rate due to AEs, we will include 48 (43/0.90) patients in each group (96 patients in total).

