### Statistical methods

#### Statistical methods for primary and secondary outcomes {20a}

Baseline assessments, outcome and safety parameters will be summarised using simple descriptive statistics. Continuous, normally distributed variables will be expressed as means and standard deviations; continuous, non-normally distributed and ordinal variables as medians (25th–75th percentiles); and categorical variables as counts and percentages. Normality of data will be explored by a Normal Q-Q Plot and tested by the Shapiro-Wilk test. Statistical uncertainties will be quantified with two-sided 95% confidence intervals. All analyses will be based on the intention-to-treat principle, whereas the primary outcome (the number of patients in remission) and three secondary outcomes (time to improvement on disability, number of patients with improvement on disability ≥ MCID, and number of (S)AEs) will be additionally analysed on per-protocol basis. A two-sided *p* value < 0.05 will be considered statistically significant. We will not correct for multiple testing. Data analyses will be performed blinded for the allocated study intervention.

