##### Safety evaluation

AEs reported or assessed during study visits in the first 24 weeks (or within 6 weeks in case of a preliminary endpoint) and AEs identified on patients’ questionnaires (week 18) will be summed up and plotted separately from adverse events reported on the physicians’ questionnaires (week 52). Frequency of (S) AEs, counted once per patient, as well as description, duration, severity score, consequences for IMP administration and outcome is summarised using descriptive statistics. Frequencies will be reported as counts (percentages), per treatment group. AEs are specified by description. Frequencies of patients reporting mild and moderate AEs (combined) and severe AEs are reported. For the physician completed week 52 AE questionnaire, frequencies of patients reporting AEs and specific AEs are reported. Frequencies will be compared between the treatment groups using the chi-square test. In case of low observed counts (< 10) or expected counts (< 5), we will use the Fischer exact test instead of the chi-square test. Frequency of SAEs along with description is reported. Frequency of patients with (S) AEs leading to change in or discontinuation of treatment protocol will be reported.

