### Adverse event reporting and harms {22}

AEs are defined as any undesirable experience occurring to a patient during the first 24 weeks of the study (treatment period + 6 weeks), whether or not considered related to study drugs (IVMP, placebo), standard care (IVIg) or co-medication (osteoporosis prophylaxis). In case study treatment is stopped before the 18-week treatment protocol is completed (i.e. in case of deterioration, switch to plasmapheresis), (S) AEs are recorded until 6 weeks after last study treatment. All AEs reported spontaneously by the patient or observed by the investigator or his staff are recorded at each follow-up visit during the treatment period. In addition, we will use structured questionnaires to assess corticosteroid and IVIg-associated AEs at 18 weeks, 52 weeks and at 104 weeks (long-term safety follow-up). In case weight gain is reported and confirmed by investigator, an increase of 3 kg or more is considered an adverse event. A SAE is any untoward medical occurrence or effect that at any dose results in death, is life threatening (at the time of the event), requires hospitalisation or prolongation of existing inpatients’ hospitalisation, results in persistent or significant disability or incapacity and is a congenital anomaly or birth defect; any other important medical event that may not result in death, be life threatening, or require hospitalisation may be considered a serious adverse experience when, based upon appropriate medical judgement, the event may jeopardise the patient or may require an intervention to prevent one of the outcomes listed above. SAEs that occur during the first 24 weeks of the study, or in the case of an early endpoint within 6 weeks of last treatment course, whether or not causally related to the treatment with IVMP must be reported immediately (within 24 h of the investigator becoming aware of the event) to the sponsor. Hospitalisation for receiving IVIg or any other CIDP treatment, such as (admittance to a hospital/day care facility for) plasmapheresis, will not be regarded a SAE. The sponsor will report the SAEs through a specific web portal (ToetsingOnline) to the accredited METC that approved the protocol, within 15 days after the sponsor has first knowledge of the SAE. SAEs that result in death or are life threatening will be reported within 7 days after the responsible investigator has first knowledge of the adverse event. Complete report is reported within 8. SAEs that occur in the UK will be also reported in the UK following national and local regulations. All AEs will be followed until they have abated, or until a stable situation has been reached. Depending on the event, follow-up may require additional tests or medical procedures as indicated, and/or referral to the general physician or a medical specialist.

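### The 3 kg weight-gain adverse event starts from a report, and the protocol does not say whether a gain found at the scheduled weighings counts without one

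*Protocol article*

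**What the plan says.** The section on adverse event reporting and harms gives weight gain its own rule: "In case weight gain is reported and confirmed by investigator, an increase of 3 kg or more is considered an adverse event". The sentence sets an order: a report, then confirmation, then the 3 kg threshold.

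Table 1 schedules body weight at baseline, week 18 and week 52, and at an unscheduled visit if that visit is a preliminary endpoint.

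Other routes exist by which a gain could be recorded:

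- General recording, in the same section: "All AEs reported spontaneously by the patient or observed by the investigator or his staff are recorded at each follow-up visit".
- Solicited report, under Outcome measures: "Patients will complete a structured questionnaire with most frequent corticosteroid and IVIg-related AEs at the 18-week visit". Table 1 places this at the same visit as the week-18 weighing. The items are not listed.
- Investigator assessment, under Outcome measures: "Long-term corticosteroid related AEs are also assessed by the investigator at weeks 52 and 104".

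The general definition is limited in time: "AEs are defined as any undesirable experience occurring to a patient during the first 24 weeks of the study". For analysis, Safety evaluation says of event frequencies: "Frequencies will be compared between the treatment groups using the chi-square test", with an exact test for low counts. It names no comparison of measured weight. The opening of the statistical methods says: "Baseline assessments, outcome and safety parameters will be summarised using simple descriptive statistics". Body weight is not mentioned there.

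**The concern.** The protocol fixes an objective cut-off and collects the measurement needed to apply it to every patient, but words the rule so that it begins with a report. Take a patient who is at least 3 kg heavier at week 18 and does not mention it. One site may treat the weighing as a staff observation and record an event. Another may read the specific weight rule as requiring a report and record nothing. Both readings are defensible.

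The number of adverse events, including corticosteroid-associated ones, is a listed secondary outcome, and whether the combination causes more or fewer of them is a secondary objective. The sample size section also justifies its large target difference partly by the adverse events that methylprednisolone may cause, so the harms comparison will weigh on how a positive result is judged. A count that depends on reporting can lose events. It can also be shifted by a patient's or physician's guess at allocation. A change calculated from scheduled weights is much less exposed to either problem.

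**Working it through.** **1. The plan's own figure.** The documents state no rate for weight gain. The only related figure is the sample size, which supplies the number per arm: "A two-group chi-square test with a 0.05 two-sided significance level will have 80% power" for 0.35 against 0.65.

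n = [1.960 × √(2 × 0.5 × 0.5) + 0.8416 × √(0.35 × 0.65 + 0.65 × 0.35)]² / 0.30² = (1.386 + 0.568)² / 0.09 = 42.4, so 43 per arm. With 10% attrition, 43 / 0.90 = 47.8, so 48 per arm. Both figures reproduce.

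**2. Which weights fall where.** The scheduled post-baseline weighings are at weeks 18 and 52. The general adverse event definition ends at week 24, so week 18 (or an earlier preliminary-endpoint visit) is the only scheduled weighing inside it. A gain first measured at week 52 can enter only through the week-52 physician questionnaire, which Safety evaluation keeps separate.

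**3. Effect of incomplete reporting, same share in both arms.** These are assumptions, not figures from the documents. Let the true rates be p₀ (placebo) and p₁ (methylprednisolone), and let s be the share of true gains that is reported. Observed rates are s·p₀ and s·p₁, and the observed difference is s·(p₁ − p₀). Power is for the two-sided Fisher exact test at 0.05 with 48 per arm, by exact enumeration. For p₀ = 10% and p₁ = 30%:

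| Share reported | Observed rates | Expected cases | Difference | Power |
|---|---|---|---|---|
| 100% | 10% v 30% | 4.8 v 14.4 | 20 points | 61.3% |
| 80% | 8% v 24% | 3.8 v 11.5 | 16 points | 46.4% |
| 60% | 6% v 18% | 2.9 v 8.6 | 12 points | 30.5% |
| 40% | 4% v 12% | 1.9 v 5.8 | 8 points | 15.4% |

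For true rates of 15% and 40%, power at the same four shares is 73.3%, 58.2%, 40.0% and 21.4%.

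**4. Different shares in the two arms.** Keep 10% v 30%.

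- Placebo share 40%, methylprednisolone share 80%: 0.4 × 10% = 4% and 0.8 × 30% = 24%. The difference stays at 20 points, but the risk ratio rises from 3 to 6.
- Placebo share 80%, methylprednisolone share 40%: 0.8 × 10% = 8% and 0.4 × 30% = 12%. The difference falls to 4 points and the risk ratio to 1.5.

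Uneven reporting can therefore distort the comparison in either direction. The power figures in step 3 do not measure it.

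**The case against.** The strongest reply is that the weight rule must be read with the sentences just before it. Those record events observed by staff, who do the weighing, and describe structured questionnaires at weeks 18, 52 and 104. On that reading, a report includes a questionnaire answer, and the 3 kg threshold only stops trivial gains from being counted. The week-18 and week-52 questionnaires coincide with weighings. Patients, treating physicians and evaluating physicians are blinded, and investigator confirmation guards against false reports. How scheduled weights are tabulated is commonly left to the analysis plan.

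Much of this stands. A reader might infer that gains count only when volunteered, and hence that this harm is under-counted. The documents do not support that: other capture routes exist, and the loss is nil if they work fully. Nor do the documents rank weight gain as a key corticosteroid harm; they mention it once. A reader might also take the power losses as a shortfall of the plan. They are not, because they rest on assumed rates and no adverse event comparison has a power target.

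What remains is the wording. The week-18 questionnaire is itself a patient report, and its items are not shown. The general observation clause and the specific weight rule point different ways for an unreported measured gain. Confirmation removes false positives but does not recover gains that nobody raised. The objection is to an event definition stated in this document, not to a missing tabulation.

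**Conclusion.** The point holds as an ambiguity in one safety definition, with a risk of missed or unevenly counted gains. It does not show that under-counting occurs. The size cannot be estimated from the documents: it is zero with complete capture. With equal incomplete capture in both arms, the risk difference shrinks in proportion to the share reported (from 20 points to 16, 12 or 8 at 80%, 60% or 40%, if the true rates were 10% and 30%). With unequal capture it could go either way. The primary outcome and the sample size are not affected. The point is minor, but worth acting on because the weights are already scheduled.

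**What to change.** For all patients, and whether or not anyone reported weight gain, derive from the scheduled weights:

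- the proportion with an increase of 3 kg or more from baseline, and the mean weight change, at week 18 or at the preliminary-endpoint visit. Compare both by arm and show them alongside the reported adverse events;
- the same two measures at week 52, presented separately with the week-52 safety data because that visit lies outside the 24-week event window.

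State in the harms section whether a measured gain counts as an event without a report. Give the number of patients weighed in each arm, since the fifth amendment described in the Discussion allowed some week-18 and week-52 visits by telephone.

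The cost is one derived variable and probably a slightly higher event count in both arms. No new visit or measurement is needed.

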
### Frequency and plans for auditing trial conduct {23}

There are no plans for an audit of trial conduct. Monitoring of study management and data collection is discussed in the section ‘Interim analyses {21b}’.

### Plans for communicating important protocol amendments to relevant parties (e.g. trial participants, ethical committees) {25}

All amendments will be submitted for approval to the MREC and to the competent authority (CA). Relevant changes to protocol and/or study management are reported to study staff and, if applicable, to participants. Trial registry is updated following substantial amendments. The study sponsor will submit a summary of the progress of the trial to the accredited MREC once a year. Information will be provided on the date of inclusion of the first patient, numbers of patients included and numbers of patients that have completed the trial, SAEs/serious adverse reactions (ARs), other issues and amendments.

## Dissemination plans {31a}

Trial results will be published in a medical scientific journal. Results will be presented during (international) conferences and events organised by patient foundations.

## Discussion

The OPTIC trial is a randomised controlled trial aiming to determine whether combined induction treatment of IVIg and IVMP leads to more remissions than IVIg treatment alone. The trial was designed with IVMP as add on treatment, as most physicians and patients prefer IVIg treatment instead of first-line corticosteroids due to its rapid mode of action and side effect profile. Alternative designs, such as IVMP treatment as standard treatment and randomisation to IVIg/placebo as add on treatment, or an IVIg versus IVMP head-to head comparison, would have reduced feasibility of including sufficient patients due to expected reluctance of patients to participate. A trial directly comparing IVIg and IVMP, with a different primary outcome and inadequate power to assess differences in remission rates, has been performed previously and these long-term remission data contribute to the rationale of the current study [9, 30]. In addition, given the expected difference in time to improvement and possibility of unblinding due to corticosteroid AEs, the design of a head-to-head comparison with a primary outcome of remission would be challenging, as patients not improving in the first 1–2 months will probably drop out of the study to be treated with IVIg. This would lead to a relatively large group stopping with corticosteroids and insufficient exposure to corticosteroids to achieve remissions, as seen in the previously mentioned study [9]. Finally, a 3-arm study of IVIg, IVMP and combined IVIg and IVMP would probably provide the best evidence and guidance, but this design would have the same challenges of including sufficient patients and of early drop-out, and was not regarded feasible in this rare disease. The IVIg regimen is a shortened version of the treatment protocol in the largest IVIg trial in CIDP [13]. This IVIg treatment protocol was chosen to limit potential efficacy concerns in the control group, which may arise from different local IVIg protocols. Local protocols vary in dosing regimens, intervals and dose tapering or withdrawal strategies. It is likely that some patients are overtreated with IVIg in this 18-week treatment protocol, as some patients may only require a single loading dose or maintenance treatment at a lower dose than 1 g/kg [31]. We aim to limit potential overtreatment by stopping treatment after 18 weeks, but if the combined induction treatment proves superior, one could consider individualising treatment by shortening the IVIg treatment and/or reduce the dose regimens depending on treatment response. The primary outcome, remission at 52 weeks, is measured using the I-RODS and the adjusted INCAT-DS. We chose to include both outcome measures to assess disability as relevant changes may be missed in patients if only one of these is used, as was shown in both the IVIg withdrawal as well as subsequent restabilization phase of the PATH study, which used a combination of both outcome measures to assess relevant changes [32, 33]. Combining two outcome measures and using a(n individual) MCID-based approach, we hope to limit potential delay when treatment is required in the event of a relapse. Precautions have been taken to limit potential side effects and unblinding, such as excluding significant cardiovascular co-morbidity and diabetes from enrolment. Potential synergistic effects of IVIg and IVMP regarding (S) AEs have not been previously mentioned in CIDP studies. A study comparing the addition of IVMP/placebo to IVIg in Guillain-Barré syndrome (GBS) did not report significant differences in (S) AEs between the two treatment arms [34]. All patients in the Netherlands will be treated with co-medication to reduce the chance of corticosteroid-induced osteoporosis. In the UK, only patients at risk will be offered co-medication (regardless of subsequent treatment allocation), following national guidelines. This is based on the fracture risk assessment (FRAX score) and counselling regarding the side effects of alendronate acid. We excluded several patient categories for safety reasons (risk of thrombosis) and high risk of unblinding (diabetes). If the combination treatment proves superior, this treatment could be considered in patients that are currently excluded, if AEs due to IVIg and/or corticosteroids are considered manageable. The OPTIC trial started enrolling participants in February 2018. Due to protracted legal negotiations and institutional review board (IRB)/MREC approval, study start was delayed in some Dutch centres as well as in the UK. In the UK, study was approved by the MHRA (Medicines and Healthcare products Regulatory Agency UK) on 29 March 2019, the South Central – Oxford REC 10 May 2019 and by the Health Research Authority (HRA) and Health and Care Research Wales (HCRW) 16 May 2019. This has resulted in a slower rate of inclusion than anticipated. Overall, most eligible patients screened for the study who meet the inclusion criteria are willing to participate in the study. Screen failures are predominantly due to the presence of diabetes, which is an exclusion criterion, or previously administered treatment. As this trial focuses on patients with active disease, instructing non-participating and referring hospitals not to start treatment for CIDP is probably one of the biggest challenges to ensure a steady rate of inclusions. Regarding trial oversight, monitoring of visits so far did not report any operational issues regarding data quality and collection or protocol adherence. The DSMB, after an SAE and after unblinded review of safety data following the first 20 inclusions, did not advise any changes to study management or safety measures. During the course of the study, five amendments were made to the protocol and overall conduct of the study. The first amendment (approved 25 May 2018) added a ‘known pulmonary embolism or other deep venous thrombosis in patient’s medical history, without current anticoagulant therapy’ to the exclusion criteria after a SAE in the first patient enrolled in the study. The DSMB charter was modified to allow for ad hoc meetings at the request of PI. The patient information sheet was changed to include specific warning signs for (deep venous or arterial) thrombosis. The protocol was changed to allow local pharmacies to source IVMP and co-medication. The second amendment (2 July 2018) implemented a change of PI in the Radboud University Medical Centre. The third amendment (15 February 2019) included a cap on the total amount of IVIg administered (standard care) of 200 g, reflecting local practices in the UK. A range of appropriate dosing was added to reflect local practices regarding co-medication dosing the UK. A window of 2 days (earlier and later) was added in the planning of home care treatment scheduling. An emergency unblinding procedure was added. A 2- and 4-week window was added for the week 52 and week 104 study visits. Language was added to specify that hospital (or day care) admittance for further CIDP treatment (in case of a relapse, deterioration during treatment protocol) would not be considered a SAE. The fourth amendment (5 August 2019) further specified the text of two exclusion criteria (4 and 11) and added a further two (5 and 6) during the process of ethical approval in the UK. These additions were not made after a SAE or other safety concerns. In the fifth amendment (15 May 2020), changes to protocol were made to ensure safe study assessments in light of the COVID-19 outbreak. Enrolment of patients was temporarily stopped. Patients in the treatment phase of the trial were allowed to continued treatment. Study visits were allowed to be conducted as a telephone consultation, with questionnaires sent by mail or through Castor EDC. Week 18 and 52 visits were conducted by phone, in clinic or as home visits (the latter two if safety permitting). The amendment included a provision which allowed for a return to normal protocol when restrictive measures were (gradually) lifted. Screening logs were maintained during the temporary enrolment stop.
